#### Withdrawal

All patients are fully informed about their participation in this study and can decide to withdraw from this trial at any time. Any information regarding patients who decide to withdraw from the protocol are excluded from the final analysis.

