### Sample size calculation

The null hypothesis is that WI is inferior to WI plus L-TAP. To test the alternative hypothesis of noninferiority of WI compared with WI plus L-TAP, the sample size is calculated using the mean value of NRS. Considering our results with previously treated patients, the mean (standard deviation [SD]) pain intensity score according to NRS is 2.8 (1.9) for the WI plus TAP block group and 3.1 (1.9) for the WI group. These data have been used for the sample size calculation. The noninferiority limit of NRS 1 has been intended to be the largest difference that is clinically acceptable, so that a difference greater than 1 would matter in practice. A two-sided sample size calculation with 0.8 power and significance level of 0.05 reveals that 100 patients have to be included. With an estimated dropout rate of 8%, a sample size of 108 patients is required with 54 patients in the WI group and 54 patients in the WI plus L-TAP group. Patient recruitment is split between the two centers. Sample size has been calculated using PASS® version 14.0.8 with a noninferiority test for the difference of two means.

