### Allocation

Patients satisfying the inclusion criteria and willing to enter the study are randomized to one of the two study arms after signing the informed consent. The randomization is performed blindly in a 1:1 fashion. The allocation to WI group or WI plus L-TAP group is achieved by creating a randomization list that includes a maximum of six subjects for nine blocks. The randomization list has been obtained by using an online program available at https://www.sealedenvelope.com/simple-randomiser/v1/lists. A separate list has been created for each center so that 54 patients are recruited at the Division of General and Hepatobiliary Surgery, University of Verona Hospital Trust, Verona, Italy, and 54 patients at the Colorectal Cancer Center, Kyungpook National University Medical Center, Kyungpook National University, Daegu, Korea. Similarly, each center collects the data separately after identifying the patients with an alphanumeric code.

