### Statistical analysis

Statistical analyses will be performed on an intention-to-treat (ITT) basis using IBM SPSS Statistics software version 21.0 (IBM Corporation, Armonk, NY, USA). Because the ITT analysis includes all randomized subjects and, in this study**,** there may be up to 6% missing data, an imputation method will be established. A per-protocol (PP) analysis will also be performed. In noninferiority studies, both ITT and PP analyses are recommended and should support the noninferiority hypothesis. Continuous variables are summarized as mean and SD or as median and 95% confidence interval (95% CI) if the distribution is asymmetrical. Categorical variables are summarized as numbers and percentages. The categorical variables will be compared between groups with the chi-square test or Fisher’s exact test, depending on the number of events. The continuous variables will be compared between groups using an unpaired *t* test or the Mann-Whitney *U* test, depending on data representation. A two-sided *P* value less than 0.05 will be considered significant.

The primary outcome considers the level of pain at 6 hr from surgery graded according to the NRS. Assuming a pain score difference of 1 of 10 to be clinically significant, noninferiority is determined when the lower boundary of the 95% CI is > 1. Superiority, on the other hand, is determined when the two means are significant at the 5% level (two-sided *P* < 0.005).

The secondary objectives aim at assessing the benefits of choosing one procedure over the other. Descriptive statistics and plots will be used to compare the two groups, taking into account: (1) pain intensity scores at 12, 24, 36, 48, and 72 hr after surgery; (2) the quantity of rescue analgesic drugs consumed from the day of surgery until POD 3; (3) the occurrence of PONV; (4) the occurrence of PPOI; (5) the time needed to restore bowel function considered as the time needed to pass gas and stool as well as to tolerate a liquid and solid diet; and (6) the length of hospital stay.

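### The withdrawal rule drops every withdrawn patient from the final analysis, which contradicts the planned ITT analysis of all randomized patients and discards 6 h pain scores already recorded

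*Protocol article*

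**What the plan says.** In the protocol article, under Interventions, Withdrawal, patients "can decide to withdraw from this trial at any time". The next sentence reads: "Any information regarding patients who decide to withdraw from the protocol are excluded from the final analysis". It is not limited to the PP set, to data after the date of withdrawal, or to patients who refuse further use of their data.

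The Statistical analysis section says: "Statistical analyses will be performed on an intention-to-treat (ITT) basis". It then describes that set: "Because the ITT analysis includes all randomized subjects". On incomplete data it adds that "there may be up to 6% missing data, an imputation method will be established". A PP analysis is also planned, and the section states that "both ITT and PP analyses are recommended and should support the noninferiority hypothesis".

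Three other sections bear on the point. Under Allocation, patients "are randomized to one of the two study arms after signing the informed consent", so withdrawal can follow randomization. Under Primary endpoint, pain is read at 6 h after surgery. Under Secondary outcome measures, pain is read again at 12, 24, 36, 48 and 72 h.

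**The concern.** The two rules give different answers to who enters the primary analysis. A set without withdrawn patients is not the set of all randomized patients.

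The practical loss is clearest for late withdrawals. A patient who leaves between 6 h and 72 h already has a primary score, so for the primary endpoint nothing is missing and there is no missing-data reason to remove that patient.

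The noninferiority setting adds to this. Asking ITT and PP to agree is useful because the two sets handle departures from the plan differently. If the withdrawal rule applies to the whole final analysis, both sets lose the same patients, and agreement says nothing about the effect of losing them. The endpoint is patient-reported pain, so withdrawal could be related to outcome and could differ between arms.

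**Working it through.** **1. The contradiction.** This needs no arithmetic. The table sets the two rules side by side by time of withdrawal.

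| Withdrawal after randomization | 6 h score | Withdrawal section | Statistical analysis section |
|---|---|---|---|
| Before surgery | none | excluded | in ITT; imputation planned for missing data |
| After surgery, before 6 h | none | excluded | in ITT; imputation planned for missing data |
| Between 6 h and 72 h | recorded | excluded | in ITT with the observed score |

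The rules disagree in every row. In the last row the withdrawal rule discards an observed primary value.

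**2. How many patients.** The Sample size calculation section gives 100 evaluable patients, 8% dropout and 108 in total, 54 per arm. The plan's figure reproduces as 100 × 1.08 = 108. That leaves 54 − 50 = 4 patients per arm as the planned loss (0.08 × 54 = 4.3). Whether 100 follows from the stated means, SD and power is a separate matter and is not used here.

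**3. Size of a possible bias (assumed pattern).** The article gives no withdrawal pattern, so the following are assumptions:
- 4 of 54 WI patients withdraw.
- Their 6 h NRS is on average D points above that of the 50 retained WI patients, with D from 1 to 4.
- Withdrawals in the L-TAP arm are unrelated to pain.
- Noninferiority is judged on WI minus L-TAP against a margin of 1 with a two-sided 95% CI, which is a one-sided level of 0.025.

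The mean of all 54 WI patients exceeds the mean of the retained 50 by (4/54) × D, and exclusion lowers the estimated difference by that amount.

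The standard error with 50 per group and the article's SD of 1.9 is 1.9 × √(2/50) = 0.38.

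If the true difference equals the margin, the chance of wrongly declaring noninferiority is Φ(shift/0.38 − 1.96).

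| D | Shift = 4D/54 | Shift/0.38 | One-sided type I error |
|---|---|---|---|
| 0 | 0 | 0 | 0.025 |
| 1 | 0.074 | 0.195 | 0.039 |
| 3 | 0.222 | 0.584 | 0.084 |
| 4 | 0.296 | 0.779 | 0.119 |

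The shift is therefore 0.07 to 0.30 NRS, against a margin of 1 and a standard error of 0.38.

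**4. Direction.** If the high-pain withdrawals are in the L-TAP arm and the WI withdrawals are uninformative, the same shifts apply with the opposite sign and work against noninferiority. If both arms show the same pattern, they cancel.

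**The case against.** The strongest reply is that the conflict is narrow and pain-driven loss before the primary reading is unlikely. The intervention is given once, during surgery; the endpoint follows at 6 h; and patients are told to request rescue analgesia when pain exceeds NRS 4. Instruction at accrual takes place 15 to 20 days before surgery, so some withdrawals may occur before the operation for reasons unrelated to pain. The withdrawal rule may also have been meant only for patients who revoke consent to the use of their data. All of this is fair. It limits the likely size of the bias and makes its direction uncertain. It does not remove the contradiction, because the sentence as written covers anyone who withdraws at any time.

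Some stronger readings do not hold:

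- A reader might infer that ITT becomes a completers analysis and that the ITT/PP check is worthless. The rule removes only patients who decide to withdraw. Protocol deviators, and patients who stay in the trial but miss the 6 h score, remain in ITT, so the two sets can still differ. The check is weakened as to withdrawals.
- A reader might set the 8% dropout against the up to 6% missing data. One inflates the sample size and the other is an upper bound on missing values; they are different quantities and need not match.
- A reader might compare the shift with the 0.25 left after subtracting the CI half-width (1 − 1.96 × 0.38 ≈ 0.25). That figure is only the upper bound of the observed differences that allow noninferiority; zero and all negative differences also qualify. The margin and the standard error are the better yardsticks.
- A reader might conclude that the rule favours noninferiority, or that data are destroyed. The article supports neither: the direction depends on who withdraws, and the text speaks of exclusion from analysis.

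That the article is condensed is no answer here. It states both rules, and a fuller document could follow only one of them.

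**Conclusion.** Wrong as written. The exclusion of withdrawn patients cannot stand beside an ITT analysis of all randomized subjects, and it discards observed primary scores of patients who leave after 6 h. This rests on the text alone.

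The size of the effect is conditional. At about the planned loss of 4 per arm, the illustration gives a bias of up to 0.30 NRS and a type I error of up to about 0.12 in place of 0.025. These figures hold only for informative withdrawal confined to the WI arm, with 50 per group and SD 1.9. With few or uninformative withdrawals the effect would be small, and with the reverse pattern it would work against noninferiority.

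**What to change.** Replace the second sentence of the Withdrawal section with: *Data collected up to withdrawal are kept and analysed in the randomized arm in the ITT analysis, unless the patient withdraws consent to their use; withdrawals are reported by arm with timing and reason.*

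In the Statistical analysis section, say that the planned imputation also covers withdrawn patients who have no 6 h score and whose data may be used. The choice of imputation method can stay with the statistical analysis plan.

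The cost is a few sentences, with no new patients or assessments. Recruitment is reported as complete, but the analyses are described as still to be performed. The wording should therefore be settled before results by arm are examined, since choosing between the two rules afterwards would itself be open to bias.

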### Outcome measures

#### Primary endpoint

To demonstrate the noninferiority of WI compared with WI plus L-TAP for pain control in the early postoperative period after laparoscopic colorectal resection. The pain control is evaluated at 6 hr from surgery considering the greatest intensity of pain at rest and during cough, according to NRS. The NRS is graded from 0 to 10, where 0 refers to “no pain” and 10 to “worst pain.”

#### Secondary outcome measures

To demonstrate the noninferiority of WI compared with WI plus L-TAP for the other short-term postoperative outcomes that could be influenced by the analgesic regimen, we will assess the following:*Pain control until POD 3*: Equal to the primary outcome, intensity of pain is evaluated according to NRS score and measured at 12, 24, 36, 48, and 72 hr from surgery.*Need for rescue analgesics*: Consumption of painkillers until 72 hr was evaluated by using the defined daily dose (DDD). The DDD is a previously validated method described by the World Health Organization that converts each pain medication into a standard unit based on drug and method of administration. The conversion formula for each drug in the study was acetaminophen intravenously (1 DDD = 3 g), tramadol intravenously (1 DDD = 300 mg), and ketorolac intravenously (1 DDD = 30 mg).*Occurrence of PONV*: PONV is assessed using a categorical scale graded from 0 to 2 where 0 refers to absence of nausea or vomiting, 1 to the presence of nausea, and 2 to the occurrence of vomiting.*Occurrence of PPOI*: PPOI is defined as the cessation of coordinated bowel motility that prevents effective transit of intestinal contents or tolerance of oral intake lasting more than 3 days and impairing the expected postoperative course. PPOI is designed as a two-variable category, where 0 means absence of PPOI and 1 means occurrence of PPOI.*Return of bowel function*: Return of bowel function is evaluated considering the time (days) needed for the bowel to open to gas and stool as well as for the patient to tolerate a liquid and solid diet.*Postoperative morbidity*: Postoperative morbidity is classified according to Clavien-Dindo classification.*Possibility to be discharged from the hospital*: Ability to go back home is computed considering postoperative length of hospital stay (days).

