## Methods/design

### Trial design

This is a prospective, randomized, controlled, two-arm, multicenter, single-blind study evaluating the efficacy of postoperative analgesic management of WI versus WI plus L-TAP in the context of laparoscopic colorectal surgery. Randomization is at the patient level, and participants are randomized 1:1 to receive either WI alone or WI plus L-TAP.

The protocol aim is to demonstrate the noninferiority of WI compared with WI plus L-TAP in terms of effectiveness of pain management. We are supposing a noninferiority limit for pain assessment measured according to the numeric rating scale (NRS) of 1 of 10 as the largest difference that is clinically acceptable, so that a difference in NRS greater than 1 would matter in practice.

Patients enrolled in this trial are asked to report their pain according to NRS at rest and during cough or movements, together with the occurrence of PONV at 6 h from surgery and twice daily until POD 3. Contemporarily, the amount of rescue analgesics is recorded, with patients being educated to request additional analgesic drugs when their pain is greater than NRS 4. Resumption of gut functions, evaluated as the passage of gas and stool as well as the ability to tolerate liquid and soft diet, is also considered together with the postoperative length of hospital stay. The study flow diagram and time of collection of outcomes are shown in Figs. 1 and 2, respectively.

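### The lead-in to the secondary outcomes sets a noninferiority aim that conflicts with the aims stated elsewhere and that the planned analysis cannot support

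*Protocol article*

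**What the plan says.** The protocol article frames the secondary outcomes in more than one way.

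- **Abstract and Study aims and objectives.** Both say that the secondary purpose is to evaluate other short-term results related to pain management. Neither mentions noninferiority.
- **Secondary outcome measures.** The lead-in is confirmatory: "To demonstrate the noninferiority of WI compared with WI plus L-TAP for the other short-term postoperative outcomes". Seven headings follow: pain to postoperative day 3, rescue analgesics, PONV, prolonged ileus, return of bowel function, morbidity and length of stay.
- **Statistical analysis, secondary paragraph.** "The secondary objectives aim at assessing the benefits of choosing one procedure over the other", and "Descriptive statistics and plots will be used to compare the two groups". The list there has six items. Morbidity is not among them, although the outcome section includes it ("Postoperative morbidity is classified according to Clavien-Dindo classification").
- **Statistical analysis, general paragraph.** Categorical variables are compared by chi-square or Fisher's exact test and continuous ones by t test or Mann-Whitney, at a two-sided 5% level.

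There is one margin in the document. Trial design says "We are supposing a noninferiority limit for pain assessment measured according to the numeric rating scale (NRS) of 1 of 10", with no time point, and Sample size calculation says "The noninferiority limit of NRS 1 has been intended to be the largest difference that is clinically acceptable". There is one noninferiority rule, "noninferiority is determined when the lower boundary of the 95% CI is > 1", and it stands in the paragraph on pain at 6 hours. Later pain is introduced with "Equal to the primary outcome, intensity of pain is evaluated according to NRS score and measured at 12, 24, 36, 48, and 72 hr".

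**The concern.** A noninferiority claim needs a margin and a rule that compares a confidence limit with it. A test of difference supplies neither, because failing to find a difference does not show that the difference is small. A reader who takes the lead-in at its word has only descriptive summaries and P values to set against it.

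The Discussion says that noninferiority of WI would call the role of TAP block into question. A noninferiority label on PONV, ileus or length of stay would strengthen that conclusion. The trial was sized on NRS pain alone, so the label could be attached to outcomes on which sizeable harm had not been excluded.

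**Working it through.** **1. Aim against analysis**

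| Outcome | Aim in the lead-in | Margin in the document | CI rule | In the secondary analysis list |
|---|---|---|---|---|
| NRS at 12 to 72 hr | noninferiority | 1 point, by inheritance | none (rule is for 6 hr) | yes |
| Rescue analgesics (DDD) | noninferiority | none | none | yes |
| PONV (0 to 2) | noninferiority | none | none | yes |
| Prolonged ileus (0/1) | noninferiority | none | none | yes |
| Bowel function (days) | noninferiority | none | none | yes |
| Morbidity (Clavien-Dindo) | noninferiority | none | none | no |
| Length of stay (days) | noninferiority | none | none | yes |

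A margin is absent for six of seven outcomes. One NRS point has no meaning on a DDD, binary, ordinal or day scale.

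**2. Precision (illustration)**

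The plan states no figure for the secondary outcomes, so there is none to reproduce. The sample size of 108, 54 per arm, is for the primary comparison; whether it follows from its inputs is a separate matter. Event rates and length-of-stay SDs below are assumptions, since the document gives none.

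Risk difference, same rate p in both arms: half-width h = 1.96 × √(2p(1−p)/54).

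- p = 0.10: 1.96 × √(0.18/54) = 0.113
- p = 0.20: 1.96 × √(0.32/54) = 0.151
- p = 0.30: 1.96 × √(0.42/54) = 0.173

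Length of stay: h = 1.96 × SD × √(2/54) = 0.377 × SD, giving 0.75, 1.13 and 1.51 days for SD 2, 3 and 4.

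With 50 evaluable per arm (the plan's 100), the risk-difference half-widths become 0.118, 0.157 and 0.180.

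**3. What a non-significant result leaves open**

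Non-significance means that the observed difference d lies within ±h. The unfavourable limit, d + h, can then approach 2h. That is about 23 to 35 percentage points (2 × 0.113 to 2 × 0.173), or 1.5 to 3.0 days (2 × 0.75 to 2 × 1.51). This treats h as fixed, which is approximate for proportions.

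**4. How often real harm would be non-significant**

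NRS, true deficit equal to the 1-point margin, SD 1.9 from Sample size calculation, 50 per arm: 1 − Φ(1/(1.9 × √(2/50)) − 1.96) = 1 − Φ(2.63 − 1.96) = 0.25. With 54 per arm it is 0.22. A rule that compares the 95% CI limit with the margin would wrongly declare noninferiority there 2.5% of the time.

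Binary outcome, assumed rates 10% against 20%, 50 per arm: 1 − Φ((0.10 − 1.96 × SE₀)/SE₁), with SE₀ = √(2 × 0.15 × 0.85/50) = 0.0714 and SE₁ = √((0.09 + 0.16)/50) = 0.0707, gives 0.71. For 10% against 15% it is 0.89; for 10% against 25% it is 0.49.

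**5. What a proper noninferiority test would need**

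Equal true rates, one-sided 0.025, 80% power, margin m: n per arm = (1.96 + 0.84)² × 2p(1−p)/m². For m = 10 points this gives 142 at p = 10% and 252 at p = 20%. For a continuous outcome with 50 per arm and no true difference, the margin would have to be at least 2.80 × √(2/50) = 0.56 SD.

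**The case against.** The other side has several fair points.

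- **The noninferiority aim is the outlier.** The Abstract, the Study aims section and the Statistical analysis section all frame the secondary outcomes without it; only one lead-in clause does not. This stands. It would be wrong to call noninferiority the settled secondary objective, and the point is an inconsistency of wording.
- **Nothing says that P > 0.05 will be read as noninferiority.** A reader might infer it from the lead-in combined with the named tests, but the document does not state it. The only noninferiority rule is a confidence-interval rule, and the secondary paragraph promises description. This also stands: the misreading is a risk, not a plan.
- **Later pain may have a margin.** A reader might conclude that no secondary outcome has one. Trial design gives the 1-point limit for pain assessment without a time point, and later pain is tied to the primary outcome, so inheritance is a fair reading. The absence is strict for six outcomes only.
- **The tests are named in general terms.** They probably cover the secondary outcomes, but the text does not say so.
- **An analysis plan may supply margins.** If absent margins were the whole complaint, this would answer it. It does not answer the conflict between two explicit statements of aim, because no analysis plan could follow both.
- **The figures rest on assumed rates and SDs.** Correct. They illustrate scale and do not measure an error in the plan.

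**Conclusion.** The point holds as a contradiction between stated aim and stated analysis. The lead-in to the secondary outcomes promises to demonstrate noninferiority on seven outcomes. The Abstract and Study aims promise only to evaluate, and the analysis section assesses benefits descriptively. Six outcomes have no margin, and the only CI rule is for 6-hour pain.

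The half-widths in the working must not be read as the limit of what a non-significant result excludes; that limit can be nearly twice as large. Both depend on the assumed event rates (10 to 30%) and SDs (2 to 4 days).

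The primary analysis and the sample size are untouched. The correction should still be made, because it settles what the trial may conclude about the secondary outcomes.

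**What to change.** In Secondary outcome measures, replace the lead-in with an aim such as: to estimate the difference between arms in the following short-term outcomes.

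In Statistical analysis:

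- report the difference or risk difference with its 95% CI for every secondary outcome, and add morbidity to the list;
- state that no noninferiority claim is made for these outcomes and that P > 0.05 is not read as noninferiority.

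If a noninferiority aim is kept for the later NRS readings, apply the same 1-point margin to them with a CI rule. State the direction explicitly: for WI minus WI plus L-TAP, where higher is worse, the upper limit must lie below +1. Say also whether all five time points must meet it.

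The cost is wording. Recruitment is complete, but the analysis is described in the future tense, and no further patients or data are needed. The sponsor gives up secondary noninferiority claims that the planned analysis could not support.

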#### Postoperative analgesia and PONV prophylaxis

The postoperative analgesic regimen is comparable between the two groups. Intravenous acetaminophen 1000 mg is administered three times per day (every 8 hr) from the day of surgery until POD 3. Tramadol 100 mg is prescribed as the first-choice rescue analgesic, whereas ketorolac 30 mg is used when tramadol does not achieve the desired effect.

PONV prophylaxis is based on the intravenous administration of metoclopramide 10 mg every 8 hr from the day of surgery until POD 3.

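### The rescue-analgesic outcome, as defined, also counts the scheduled acetaminophen given to both arms, which contradicts its label and the analysis section

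*Protocol article*

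**What the plan says.** Three sections of the protocol article bear on this outcome.

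- **Postoperative analgesia and PONV prophylaxis.** Acetaminophen is background treatment: "Intravenous acetaminophen 1000 mg is administered three times per day (every 8 hr) from the day of surgery until POD 3". Of the two arms the section says: "The postoperative analgesic regimen is comparable between the two groups". Rescue is a separate step: "Tramadol 100 mg is prescribed as the first-choice rescue analgesic", with ketorolac 30 mg if tramadol does not suffice.
- **Secondary outcome measures.** Under the label of need for rescue analgesics, the definition reads: "Consumption of painkillers until 72 hr was evaluated by using the defined daily dose (DDD". Three conversions follow: "acetaminophen intravenously (1 DDD = 3 g", "tramadol intravenously (1 DDD = 300 mg" and "ketorolac intravenously (1 DDD = 30 mg". Scheduled doses are not excluded.
- **Statistical analysis.** The quantity to be compared is "the quantity of rescue analgesic drugs consumed from the day of surgery until POD 3".

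**The concern.** The label and the analysis section describe rescue use. The definition between them describes painkiller consumption and gives a conversion factor for a drug that has no rescue role anywhere in the article. An analyst who follows the definition literally computes total analgesic intake. One who follows the analysis section computes something else.

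The choice matters. Rescue need is among the stated secondary aims, and the Background says that the main advantage of TAP block in the group's previous nonrandomized studies was reduced opioid use. If the rescue score consists largely of a background drug common to both arms, the arms look more alike in relative terms. If the background amount varies between patients, a real difference in rescue is also harder to detect. In a trial whose hypothesis is that the block adds little, either effect could be misread as support.

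**Working it through.** The article states no total DDD figure, so there is none to reproduce. The conversions can be worked through directly.

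**Inputs from the article**
- Acetaminophen: 1 g every 8 h; 3 g = 1 DDD.
- Tramadol rescue: 100 mg; 300 mg = 1 DDD.
- Ketorolac rescue: 30 mg; 30 mg = 1 DDD.
- Evaluable patients: 100, so 50 per arm (Sample size calculation).

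**Weight of one dose** (dose divided by the amount per DDD)
- Scheduled acetaminophen: 1/3 = 0.33 DDD.
- Tramadol rescue: 100/300 = 0.33 DDD.
- Ketorolac rescue: 30/30 = 1 DDD.

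In a summed score, one omitted scheduled dose therefore cancels one tramadol rescue, and three cancel one ketorolac rescue.

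**Score of a patient with no rescue**
- 72 h at 8-hourly dosing: 9 doses, 9 g / 3 g = 3.0 DDD.
- 10 doses, if both ends of the window count: 10/3 = 3.33 DDD.
- 12 doses, if surgery day to POD 3 means four full calendar days: 12/3 = 4.0 DDD.
- Tramadol and ketorolac only: 0 DDD.

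**Relative difference.** Suppose rescue is 1.0 DDD in one arm and 0.5 in the other.
- Rescue only: (1.0 − 0.5)/1.0 = 50% lower.
- With 3 DDD added to both: (4.0 − 3.5)/4.0 = 12.5% lower.
- The absolute difference is 0.5 DDD in both cases.

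**Absolute difference and tests.** If everyone receives the same number of scheduled doses, a constant is added. Mean differences, SDs and ranks do not change, and no power is lost.

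**If doses received vary.** The article does not give the variation, so everything here is assumed:
- 50 per arm, Poisson tramadol counts with means 1.0 and 1.7, and no ketorolac.
- Scheduled doses uniform around 9, independent of arm and of rescue use.
- Mann-Whitney test at two-sided 0.05, 10,000 simulated trials per row.

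| Scheduled doses received | Power |
|---|---|
| No variation | 0.83 |
| 0 or 1 dose missed | 0.75 |
| Plus or minus 1 | 0.64 |
| Plus or minus 2 | 0.43 |

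Repeat runs move these by about 0.01 to 0.02.

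A normal approximation for the difference in means gives a hand check. In doses, SE = √[(1.0 + 1.7 + 2v)/50], where v is the variance of the scheduled doses.
- v = 0: SE = 0.232, 0.7/SE = 3.01, power Φ(3.01 − 1.96) = 0.85.
- v = 2/3 (plus or minus 1): SE = 0.284, ratio 2.46, power 0.69.
- v = 2 (plus or minus 2): SE = 0.366, ratio 1.91, power 0.48.

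The pattern is the same, at slightly higher values than for the rank test.

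**Discharge inside the window.** If intravenous dosing stops at discharge, a patient who leaves 24 h before the window closes loses 3 scheduled doses, or 1 DDD. That equals three tramadol rescues. If discharge timing differed by arm, this would be bias as well as noise. The article does not say how often it occurs.

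**The case against.** The strongest reply has four parts.

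1. **A constant cancels.** The schedule is fixed and described as comparable between the arms. This stands for absolute differences and rank tests, provided that doses received are equal. It does not rescue the level of the score or any relative comparison.
2. **The intent is visible.** The analysis section speaks of rescue drugs, and the article never says that the DDDs are added together. The conversion list might simply cover every drug in the study. This is a fair account of what was probably meant, and it makes the correction easy. The conflict remains, because the list stands under the rescue outcome, begins with acetaminophen and excludes nothing.
3. **The consequences are limited.** The trial is powered on the pain score alone, and the analysis section plans descriptive statistics and plots for the secondary objectives. No relative reduction is announced. This stands, and it limits the weight of the power figures.
4. **The two window wordings probably mean the same thing.** The article itself uses POD 3 as the heading for pain scores taken up to 72 h. This largely stands, so the 4.0 DDD figure is an outer reading only. A single stated window would settle it.

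A reader might go further and infer that variation in scheduled doses does hide rescue differences in this trial. The documents do not support that. They report no missed doses, no discharge before 72 h and no dose variance, so the loss could be nil, small or large.

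**Conclusion.** The definition does not measure the outcome it names. If the listed drugs are summed, it measures total analgesic intake, with a floor of about 3 DDD for patients who need no rescue and equal weight for a scheduled acetaminophen dose and a tramadol rescue dose. Relative differences shrink: 50% becomes 12.5% in the example above. This part follows from the article's own conversions and schedule, and the only assumption is summation.

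Masking of a real difference is conditional. It needs variation in the scheduled doses actually received, and bias further needs that variation to differ by arm. Under the assumed inputs, power goes from about 0.83 with no variation to about 0.64 with plus or minus one dose and about 0.43 with plus or minus two. These figures illustrate sensitivity and do not estimate what happened. The primary endpoint is not touched.

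**What to change.** Reconcile the postoperative analgesia, secondary outcome and statistical analysis sections:

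- Derive need for rescue analgesics from the DDDs of the two drugs that the protocol names as rescue, tramadol and ketorolac.
- State one window in both the outcome definition and the analysis section.
- Report scheduled acetaminophen separately, as receipt of the background regimen. If total analgesic consumption is also of interest, report it as a further outcome under its own label.

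The cost is a line or two of text and a change to one derived variable. Recruitment is complete, but treatment and data collection are not affected. No new data should be needed, because converting to DDDs already requires the amount of each drug. That is an inference, since the datasheet (Additional file 2) is not shown, and it should be confirmed.
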